#### Secondary hypothesis (H2)

COS-P will enhance the quality of the relationship between foster carers and foster children, as evidenced by improvements in both dyadic interactions and overall relationship quality. Improvements in overall relationship quality will be assessed quantitatively using the Parenting Stress Index - IV - Short Form (PSI), while the Marschak Interaction Method (MIM) coded with the Dyadic Emotional Interaction Style (D-EIS) will be used to provide a complementary qualitative assessment of dyadic interactions. In addition to testing these hypotheses, the study will address the following objectives.

#### To explore potential moderators of intervention outcomes

This will include examining the influence of foster carer burnout, emotional support provided by Child Protection Services, and fidelity of program implementation.

#### To assess qualitatively the subjective experiences of participants

Focus groups and self-confrontation interviews will be conducted with foster carers and social workers who facilitated the COS-P program to gain a deeper understanding of their experiences with the intervention.

#### To assess potential iatrogenic effects

The study will carefully monitor for any unintended negative consequences of implementing COS-P within the french foster care system.

### Participants

#### Foster carers

The study will recruit foster carers from the 170 individuals employed by CPS and two accredited private foster care agencies in Haute-Loire, France (La Renouée and Mazel-Entraide Union). All foster carers will be offered the opportunity to participate in COS-P as part of their continuing education program. However, only those who meet the following criteria will be included in the study:

### Eligibility criteria

Signed informed consent form.Commitment to attend all eight sessions of the COS-P program.Employed by CPS Haute-Loire or by one of the two participating private agencies.

#### Foster children

Children will participate in the dyadic interaction assessment.

### Eligibility criteria

Placed with a foster carer participating in the study.Aged from 1 to 6 years.In permanent placement (5 or more days per week with the foster carer).Consent obtained from all individuals holding parental responsibility.

Recruitment will be completed by June 30, 2025.

#### Consent procedures

Two informational sessions will be held to present the COS-P training program and the research study. Foster carers will have the opportunity to provide consent online following these sessions. To obtain consent for the participation of children in the video-recorded assessments, placement services will contact those holding parental responsibility. Caseworkers will provide parents with a consent form, an informational brochure, and a link to an informational video.

### Study design and procedure

#### Randomized controlled trial design

This study will utilize a randomized controlled trial design with a mixed-methods approach. Participants will be randomly assigned to either the intervention group (receiving COS-P in addition to Treatment as Usual) or the waitlist control group (receiving Treatment as Usual only).

#### Treatment as usual (TAU)

Both groups will continue to receive Treatment as Usual (TAU), which consists of Psycho-Educational Support (PES) provided by CPS. PES typically involves home visits, educational and psychological support for foster carers and/or children in placement, and efforts to support and monitor contact between children and their birth families. The control group will be placed on a waiting list to receive the COS-P program as part of continuing education at a later date.

#### Circle of security parenting (COS-P) intervention

The intervention group will participate in the COS-P program in addition to TAU. Foster carers will be assigned to groups of 8 to 10 participants and will attend sessions in dedicated training facilities. The eight 2-hour sessions (detailed in Appendix 3) will be co-facilitated by two child protection professionals certified by Circle of Security International. If a participant misses a session, a 30-minute individual make-up session will be offered before the next group meeting.

#### Fidelity

To ensure fidelity to the COS-P model, all facilitators will be certified in the program after receiving four days of training. They will complete a fidelity checklist after each session, using the form provided in the intervention manual. Two group supervision sessions will be provided by a trainer accredited by Circle of Security International.

#### Randomization

A simple randomization procedure will be conducted at T0 by an independent researcher not involved in the study, using computer-generated random allocation.

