### Data collection and security

Data acquisition and management will be conducted by trained researchers, including psychologists, research engineers, and master’s and doctoral level psychology students. All data will be anonymized or pseudonymized. Data will be collected from multiple sources: online questionnaires completed by foster carers, video recordings of interactions between foster carers and children, and anonymized transcripts derived from individual interviews and focus group discussions. For data security, all pseudonymized and anonymized data will be stored on secure servers specifically designed for the management of sensitive health information. All data management procedures will adhere to the standards established by the European General Data Protection Regulation (GDPR).

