### Measures

#### Three-time measurement

Following an initial phase (T0), data collection will occur at three time points (see Table 3):

**T1 (Baseline)** Questionnaires, interviews, and interaction assessments will be administered in the week prior to the first COS-P session.

**T2 (3-month f/u)** Questionnaires, interviews, and interaction assessments will be administered three months after the final COS-P session.

**T3 (Qualitative Data Collection at 4-month f/u)** Focus groups will be conducted four months after the completion of the intervention (see Table 4 for an overview of assessments).

**Table 3 Tab3:** SAFE FAMILIES study data collection schedule

	(T0) Enrollment and allocation	(T1) Baseline	COS-*P* group (intervention arm only)	(T2) 3-month f/u	(T3) 4-month f/u
Foster Parent Consent	X				
Biological Parent Consent (video recording)	X				
Sociodemographic and Professional Questionnaire	X				
*Quantitative assessments*					
CCQ		X		X	
PSI		X		X	
PBA		X		X	
SAQ		X		X	
MSPE		X		X	
MIM-DEIS		X		X	
PDI-R		X		X	
COS-P Fidelity Log			X		
*Qualitative assessments*					
Self-Confrontation Interviews		X		X	
Focus-groups					X

**Table 4 Tab4:** Overview of qualitative and quantitative assessments

	Control Group (Gc) + Intervention Group (Gi) *N* = 70	Subgroups of Gi
	Quantitative assessments	Qualitative assessments
**Primary Outcome** Assess foster parent caregiving sensitivity and reflective functioning	CCQ	PDI-R (*N* = 20) Self-confrontation Interviews (*N* = 6)
**Secondary Outcome** Assess the relationship between the foster parent and the child		
	PSI	SMRC (*N* = 20), MIM-DEIS (*N* = 20) Focus Groups

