#### Primary outcome

**Caregiving composite questionnaire (CCQ).** The CCQ is a 43-item self-report measure specifically designed to assess parent capacities targeted by the COS-P program [28], namely: parental mentalizing, parenting self-efficacy, and parent perceptions of the child. It combines six subscales and one single item drawn from previously validated measures, retaining the original response formats and scoring procedures for each subscale. The subscales are: (a) Parental Mentalizing (18 items; e.g., *I think about what my child may be thinking or feeling*; α = 0.81); (b) Parenting Self-Efficacy - Empathy (6 items; e.g., *I am able to put myself in my child’s shoes*; α = 0.87); (c) Parenting Self-Efficacy - Affection (9 items; e.g., *I am able to show affection to my child*; α = 0.75); (d) Caregiving Helplessness (7 items; e.g., *When I am with my child*,* I often feel out of control*; α = 0.86) and (e) Parent Perceptions of the Child - Hostility (5 items; e.g., *When this child cries*,* he/she gets on my nerves*; α = 0.89. The CCQ has demonstrated good reliability and validity in a pilot sample of parents [29] and is being used in the current study to assess the impact of COS-P on these key parenting capacities. This questionnaire has also undergone validation with a sample of *N* = 1181 French foster carers as part of a larger research project on foster care conducted by our research team. Results are currently being prepared for publication.

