### Statistical analyses

***Sample size and analysis.*** Sample size calculation was based on an effect size of *d* = 0.38, drawn from a meta-analysis examining the impact of attachment-based interventions on parental sensitivity [49]. An a priori power analysis using G*Power software [50] indicated that 58 participants are needed to achieve 80% power with a significance level of *p* <.05. To account for potential attrition (20%), we aim to recruit 35 participants for each group (intervention and waitlist control receiving TAU).

The data will be analyzed using both quantitative and qualitative methods. Statistical analyses will be conducted using R software. All tests will be two-tailed with a significance level set at *p* <.05.

***Quantitative analyses.*** Descriptive statistics will be used to characterize the sample at baseline (T1) and at each assessment point (T2, T3). This will include frequencies and percentages for categorical variables (e.g., gender) and means and standard deviations for continuous variables (e.g., age, duration of placement). To test the primary hypothesis (H1), a two-way mixed ANOVA will be conducted with Group (Intervention vs. Control) as the between-subjects factor and Time (T1, T2) as the within-subjects factor. The dependent variable will be the CCQ score. To test the secondary hypothesis (H2), a two-way mixed ANOVA will be conducted with Group (Intervention vs. Control) as the between-subjects factor and Time (T1, T2) as the within-subjects factor. The dependent variable will be the PSI score. To explore the potential moderating effects of parental burnout (PBA), perceived emotional support from placement services (SAQ) and fidelity of program implementation, hierarchical multiple linear regressions will be performed. The CCQ and PSI scores at T2 will be the dependent variables, with group allocation (Intervention vs. Control) as the primary predictor. The potential moderators (PBA, SAQ, and fidelity of implementation) will be entered in the model after the main effect of group allocation.

Complementary Analyses for a Subgroup of Foster Carers: A subgroup of 20 foster carers will participate in additional assessments using the Parent Development Interview - Revised (PDI-R) and the Marschak Interaction Method (MIM) coded with the Dyadic Emotional Interaction Style (D-EIS). These assessments will be conducted at T1 (baseline) and T2 (3-month follow-up).

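### Allocation is made at T0 but the self-reported baseline is first taken at T1, so carers probably know their arm when they give the baseline that enters the Group × Time test

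*Protocol article*

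**What the plan says.** The Randomization section of the protocol article states: "A simple randomization procedure will be conducted at T0 by an independent researcher not involved in the study". Table 3 agrees: its first column is labelled "T0) Enrollment and allocation", and the only form listed there besides the consents is the "Sociodemographic and Professional Questionnaire".

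The section on the three measurement times puts T0 before all outcome measurement: "Following an initial phase (T0), data collection will occur at three time points". Of T1, the baseline, it says: "Questionnaires, interviews, and interaction assessments will be administered in the week prior to the first COS-P session". In Table 3 the CCQ, PSI, PBA and SAQ are first ticked at T1.

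The primary outcome is reported by the carer: "The CCQ is a 43-item self-report measure specifically designed to assess parent capacities targeted by the COS-P program". Data collection and security lists "online questionnaires completed by foster carers" among the data sources. Controls receive usual support and wait for the programme. The only blinding described in the available text is that of the video coding in a subgroup of dyads. Under Statistical analyses, H1 (CCQ) and H2 (PSI) are each tested by a mixed ANOVA with Group and Time (T1, T2) as factors.

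**The concern.** A baseline should be fixed before anyone can react to the allocation. Here the order is reversed, for outcomes that the carers rate themselves in a trial where their arm cannot be hidden. A carer who has been given a place may answer more hopefully, or more self-critically, than one who has been told to wait.

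The T1 score is one of the two values in the Group × Time contrast. A shift in T1 answers caused by knowing the arm is therefore read as part of the change attributed to COS-P, unless the same shift is present at T2. The PBA and SAQ, which are planned as moderators, follow the same order, so they too are first measured after allocation.

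**Working it through.** **Order of steps**

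| Step | When | Source |
|---|---|---|
| Consent, sociodemographic form, allocation | T0 | Randomization; Table 3 |
| First CCQ, PSI, PBA, SAQ | T1, in the week before session 1 | Three-time measurement; Table 3 |
| Sessions, in groups of 8 to 10 | After T1 | COS-P intervention section |
| Second CCQ, PSI, PBA, SAQ | T2, 3 months after the last session | Three-time measurement; Table 3 |

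The text and the table agree, so this is a fixed schedule and not a slip in one place.

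**Do carers know their arm at T1?** No section says when they are told. Three facts point to yes. T1 falls within a week of the first session. Intervention carers must by then have been placed in groups and given dates. Nothing in the available text holds the allocation back. This is a strong inference, not a stated fact.

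**How a T1 shift enters the test.** With two time points, the Group × Time effect is

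(T2 − T1 in intervention) − (T2 − T1 in control).

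Let knowing the arm move the difference between arms by s1 at T1 and by s2 at T2. Then bias = s2 − s1. If s2 = 0, the whole of s1 enters with its sign reversed. If s2 = s1, it cancels.

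**The plan's own sample size, for scale.** Inputs from Statistical analyses: d = 0.38, 80% power, two-sided 0.05, N = 58. Assumption not in the article: correlation between T1 and T2 of 0.5. For the within-between interaction, with f = 0.38/2 = 0.19 and 2 time points:

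λ = 58 × 0.19² × 2 / (1 − 0.5) = 8.38, power 0.812.

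N = 56 gives 0.798, so 58 is reproduced. It does not depend on whether the baseline precedes allocation.

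**Illustration of the bias.** Assumptions: unit SD at each time and correlation 0.5, so SD of change = √(2 × (1 − 0.5)) = 1; 29 per arm (58/2); no true effect; shift b at T1 in one arm and none at T2. The noncentrality is b × √(29/2) = 3.81b on 56 degrees of freedom.

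| Assumed T1-only shift b (SD) | Noncentrality | Two-sided type I error |
|---|---|---|
| 0 | 0 | 5.0% |
| 0.05 | 0.19 | 5.4% |
| 0.10 | 0.38 | 6.6% |
| 0.20 | 0.76 | 11.6% |

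The shifts are assumed; the article gives nothing from which to estimate them.

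**The case against.** The strongest reply is that the article never says carers know their arm at T1. Generating an allocation at T0 is not the same as disclosing it, and some text adjoining the Randomization section was not in the copy available, so a statement there cannot be ruled out. This stands, and it limits the point to a probable exposure. If the allocation is in fact held back until the T1 forms are in, one sentence would settle the matter.

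A second reply also stands: a reporting shift that persists unchanged to T2 cancels in the difference of changes. The one-for-one transfer is the case s2 = 0, not a general rule. An earlier baseline removes s1 only; s2 remains, as in any open trial with a self-reported outcome.

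Three stronger readings are tempting, and the documents do not support them.

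- A reader might divide the assumed shifts by the planned 0.38 and report 26% and 53% of the effect. N = 58 is reproduced with f = 0.19 and correlation 0.5. With an SD of change of 1, that implies a difference in change of 0.76 SD (0.76² × 58/4 = 8.38). The same shifts are then 13% and 26%, and they are still assumptions.
- A reader might infer that carers lost between T0 and T1 are a further bias that earlier forms would cure. Such carers would have no T1 score, but a complete-case T1/T2 ANOVA also needs T2, so an earlier baseline alone does not bring them back. The T0–T1 interval is not given and no number lost can be derived. Missing-data handling is commonly left to the full protocol or SAP.
- A reader might infer that simple randomisation contradicts the group sizes. The article's wording is "we aim to recruit 35 participants for each group", which is an aim. An exact 35/35 split has probability 9.5%, and 40/30 or more uneven has 28%. But 40/30 keeps 4 × 40 × 30/70 = 68.6 effective carers of 70, a loss of about 2%. A restricted or stratified list would be a separate, minor preference.

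**Conclusion.** The point holds as one about the order of steps. The schedule places the self-reported baseline for the primary and quantitative secondary outcomes after allocation, in a trial where carers cannot be blinded, and the available text has no safeguard against carers knowing their arm at T1. Any allocation-driven shift at T1 not matched at T2 biases the Group × Time effect and could create or mask an effect.

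The size cannot be determined from the article. For assumed T1-only shifts of 0.1 to 0.2 SD, type I error would be about 6.6% to 11.6%, given 29 per arm, an SD of change of 1 and no true effect. This is an avoidable weakness that should be corrected. It does not show that the result will be biased, and it does not invalidate the trial.

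**What to change.** Amend the Randomization section, the description of T0 and T1, and Table 3 so that the CCQ, PSI, PBA and SAQ are completed online before the allocation is generated or released. There are two ways to do this:

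- take them at T0, with the sociodemographic questionnaire already collected there, and release the allocation only after submission; or
- keep them at T1 and hold the allocation until they are submitted.

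State which option applies and when carers are told their arm. If the allocation is already withheld until T1 is complete, say so; no other change is then needed.

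The first option lengthens the interval between baseline and first session by an amount that cannot be judged, because the T0–T1 gap is not stated. The second leaves less time to form and schedule the groups, since T1 falls in the last week before they start. Neither changes the sample size of 58 or adds a questionnaire.

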### Data collection and security

Data acquisition and management will be conducted by trained researchers, including psychologists, research engineers, and master’s and doctoral level psychology students. All data will be anonymized or pseudonymized. Data will be collected from multiple sources: online questionnaires completed by foster carers, video recordings of interactions between foster carers and children, and anonymized transcripts derived from individual interviews and focus group discussions. For data security, all pseudonymized and anonymized data will be stored on secure servers specifically designed for the management of sensitive health information. All data management procedures will adhere to the standards established by the European General Data Protection Regulation (GDPR).

### Measures

#### Three-time measurement

Following an initial phase (T0), data collection will occur at three time points (see Table 3):

**T1 (Baseline)** Questionnaires, interviews, and interaction assessments will be administered in the week prior to the first COS-P session.

**T2 (3-month f/u)** Questionnaires, interviews, and interaction assessments will be administered three months after the final COS-P session.

**T3 (Qualitative Data Collection at 4-month f/u)** Focus groups will be conducted four months after the completion of the intervention (see Table 4 for an overview of assessments).

**Table 3 Tab3:** SAFE FAMILIES study data collection schedule

	(T0) Enrollment and allocation	(T1) Baseline	COS-*P* group (intervention arm only)	(T2) 3-month f/u	(T3) 4-month f/u
Foster Parent Consent	X				
Biological Parent Consent (video recording)	X				
Sociodemographic and Professional Questionnaire	X				
*Quantitative assessments*					
CCQ		X		X	
PSI		X		X	
PBA		X		X	
SAQ		X		X	
MSPE		X		X	
MIM-DEIS		X		X	
PDI-R		X		X	
COS-P Fidelity Log			X		
*Qualitative assessments*					
Self-Confrontation Interviews		X		X	
Focus-groups					X

**Table 4 Tab4:** Overview of qualitative and quantitative assessments

	Control Group (Gc) + Intervention Group (Gi) *N* = 70	Subgroups of Gi
	Quantitative assessments	Qualitative assessments
**Primary Outcome** Assess foster parent caregiving sensitivity and reflective functioning	CCQ	PDI-R (*N* = 20) Self-confrontation Interviews (*N* = 6)
**Secondary Outcome** Assess the relationship between the foster parent and the child		
	PSI	SMRC (*N* = 20), MIM-DEIS (*N* = 20) Focus Groups
**Exploratory Outcomes**		
Investigate the role of parental burnout and emotional support	PBA SAQ	Focus Groups, Self-Confrontation Interviews (*N* = 6)
Evaluate participants’ subjective experiences		

#### Primary outcome

**Caregiving composite questionnaire (CCQ).** The CCQ is a 43-item self-report measure specifically designed to assess parent capacities targeted by the COS-P program [28], namely: parental mentalizing, parenting self-efficacy, and parent perceptions of the child. It combines six subscales and one single item drawn from previously validated measures, retaining the original response formats and scoring procedures for each subscale. The subscales are: (a) Parental Mentalizing (18 items; e.g., *I think about what my child may be thinking or feeling*; α = 0.81); (b) Parenting Self-Efficacy - Empathy (6 items; e.g., *I am able to put myself in my child’s shoes*; α = 0.87); (c) Parenting Self-Efficacy - Affection (9 items; e.g., *I am able to show affection to my child*; α = 0.75); (d) Caregiving Helplessness (7 items; e.g., *When I am with my child*,* I often feel out of control*; α = 0.86) and (e) Parent Perceptions of the Child - Hostility (5 items; e.g., *When this child cries*,* he/she gets on my nerves*; α = 0.89. The CCQ has demonstrated good reliability and validity in a pilot sample of parents [29] and is being used in the current study to assess the impact of COS-P on these key parenting capacities. This questionnaire has also undergone validation with a sample of *N* = 1181 French foster carers as part of a larger research project on foster care conducted by our research team. Results are currently being prepared for publication.

**Parent Development Interview – Revised (PDI-R).** This semi-structured interview consists of 31 questions, administered in approximately one hour, covering four domains: (a) perception of the child (e.g., “What are some of your child’s strengths?”), (b) perception of the relationship (e.g., “What are some of the things you enjoy doing together?”), (c) parental affective experience (e.g., “How does it feel to be separated from your child?”), and (d) separation experiences (e.g., “Tell me about experiences of separation from your own parents when you were a child”). These domains assess reflective functioning (RF) in relation to the self (as a foster carer in this context) and the child. Parental reflective functioning (PRF) will be rated using the system developed by Slade et al. [30–32], on a scale from 1 (negative reflective functioning: rejection of mental states) to 9 (exceptional reflective functioning). The version used in this study is the French translation by Ensink et al. [33], following the translation/back-translation method described by Behling and Law [34]. The PDI-R is a well-validated measure of PRF and will be administered to a subgroup of foster carers.

